# Efficacy of amoxicillin/clavulanic acid after surgical drainage of perianal abscess in the prevention of the development of anal fistula (PERIQxA study): study protocol for a multicenter randomized, double-blind clinical trial

**DOI:** 10.1186/s13063-024-07922-3

**Published:** 2024-02-15

**Keywords:** Perianal, Fistula-in-ano, Abscess, Antibiotics, Quality of life, Colorectal surgery

## Abstract

**Background:**

Anorectal fistula, which is a relatively common pathology, is the chronic manifestation of the acute perirectal process that forms an anal abscess. The development of a fistula after incision and drainage of an anal abscess is seen in approximately 26–37%. Its treatment is a relevant topic, and the role of the use of antibiotic therapy in its prevention remains controversial, after the publication of several studies with contradictory results and several methodological limitations. Our hypothesis is that the combination of amoxicillin and clavulanic acid will reduce the incidence of anal fistula.

**Method:**

The aim of this study is to evaluate the efficacy of antibiotherapy after surgical drainage of perianal abscess in the development of perianal fistula. The PERIQxA study is a multicenter, randomized, double-blind controlled trial. The study has been designed to include 286 adult patients who will be randomly (1:1) assigned to either the experimental (amoxicillin/clavulanic acid 875/125 mg TDS for 7 days) or the control arm (placebo). The primary outcome measure is the percentage of patients that develop perianal fistula after surgery and during follow-up (6 months).

**Discussion:**

This clinical trial is designed to evaluate the efficacy and safety of amoxicillin/clavulanic in the prevention of perianal fistula. The results of this study are expected to contribute to stablish the potential role of antibiotherapy in the therapeutics for anal abscess.

**Trial registration:**

EudraCT Number: 2021–003376-14. Registered on November 26, 2021.

**Supplementary Information:**

The online version contains supplementary material available at 10.1186/s13063-024-07922-3.

## Background

An anorectal fistula (AF), also known as fistula-in-ano, is the chronic manifestation of the acute perirectal process that forms an anal abscess (AA). AA and AF should be considered the acute and chronic phase of the same anorectal disease [1]. It is a relatively common pathology and has an incidence of 3–4 and 1.04–8.6 per 100,000 cases every year in Spain and Europe respectively [2, 3]. Being an underdiagnosed pathology, its prevalence is probably even higher than estimated.

The cryptoglandular hypothesis states that AF develops from the blockage of anal glands and the perpetuation of chronic inflammation that predisposes fistula formation [4]. Between 26 and 37% of AF is diagnosed after surgical drainage of the abscess, most appearing in the first 3 months of postoperative follow-up [5, 6].

The development of fistula after drainage is associated with longer hospital stays, higher medical expenses, and patient discomfort [7]. AF manifests as an abnormal tract between the anorectal canal and the perianal skin and clearly affects patients’ quality of life [8]. Patients may experience rectal pain and pruritus, and the perianal skin may be excoriated and inflamed [9].

Perianal fistulous disease usually affects patients’ quality of life, especially in cases of long term or complex perianal fistulas [2, 10].

The treatment of abscess and fistula of cryptoglandular origin continues to be a relevant general surgery topic [11]. Historically, adjuvant antibiotic treatment has been limited to immunocompromised patients or those who presented with extensive cellulitis or sepsis [12]. The use of antibiotics in the development of AF after incision and drainage of an AA remains controversial. Published data are limited and sometimes contradictory. Different observational studies have been conducted with heterogeneous results [7, 13–15]. Only two randomized clinical trials have evaluated the prophylactic use of antibiotics in this setting [5, 6].

Considering the debate on the role of postoperative antibiotic therapy for patients with perianal abscesses and the importance of the prevention of anal fistulas, we have designed this study with the objective of determining the efficacy of antibiotherapy in preventing progression to perianal fistula, after surgical drainage of a perianal abscess.

Our hypothesis is that the combination of amoxicillin and clavulanic acid will reduce the incidence of anal fistula.

### Objectives

The aim of this trial is to evaluate the efficacy of antibiotherapy in the development of perianal fistula, after surgical drainage of perianal abscess.

### Study design

This is a phase 4, parallel group, randomized, double-blind, controlled, superiority, multicenter clinical trial. The protocol has been designed in accordance with the SPIRIT (Standard Protocol Items: Recommendations for Interventional Trials) guidelines (Supplementary Material).

Two hundred eighty-six patients (143 per arm) with perianal abscess requiring surgery will be enrolled from four different centers. Individuals fulfilling selection criteria will be randomized to receive amoxicillin/clavulanic acid or placebo at a ratio of 1:1.

## Methods: participants, interventions, and outcomes

### Participating centers

Study clinical sites included 4 public and private tertiary hospitals across different regions in Madrid (Spain). The only requirement for the participating study centers was to have a local research team with a general surgeon as principal investigator.

### Eligibility criteria

Inclusion criteria are as follows:Male or female adult patients (18 or older)First episode of perianal abscessOral feedingWillingness and ability to comply with scheduled visits, treatment plan, laboratory tests, and other study proceduresSigned written informed consent in accordance with ICH/GCP and local legislation, obtained prior to any study procedure

Exclusion criteria are as follows:Allergy or intolerance to amoxicillin/clavulanic acidContraindication to undergo any of the study proceduresHistory of previous perianal surgeryAny clinical condition, and/or analytical alteration that, *according to the investigator*, is considered significant enough to not participate in the study. The following are considered as such:Previous perianal fistula or fistula diagnosed during surgeryComplex abscessMarked cellulitis after surgical drainageHistory of inflammatory bowel diseaseHistory of anal cancerPrevious local trauma or radiotherapyDiabetes mellitusImmunosuppressed: oncology patients, chronic corticosteroid treatment or other immunosuppressants, chronic kidney diseaseProsthetic valvesMorbid obesity (BMI > 40)Signs of severe sepsisWomen with positive pregnancy test result or currently breastfeedingUnwillingness or inability to follow the procedures described in the protocolInability to give written informed consent

### Informed consent

Investigators will obtain the subject’s informed consent in accordance with Spanish Law 14/2007 on Biomedical Investigation and the internationally ethical accepted guidelines. Eligible patients may only participate in the study after providing written informed consent approved by the research ethics committee. These forms are available from the corresponding author on request. Informed consent must be obtained before performing any specific study procedure. The process to obtain informed consent should be documented in the patient’s source documents (medical history).

## Study intervention

### Intervention description

Included patients who are randomized to the experimental group will receive amoxicillin/clavulanic acid, which will be administered orally at the doses and dosing regimen given in the Summary of Products Characteristics (SmPC): 875 mg/125 mg administered three times daily for 1 week.

Included patients who are randomized to the control group will receive PLACEBO tablets, to be administered three times daily for 1 week.

### Treatment assignment method

Randomization is 1:1 and will be performed using the eCRF.

### Masking

This is a double-blind study in which neither the patient nor the research team will know whether the patient has been randomized to the control or experimental group.

### Participant timelines

The schedule of interventions and visits can be found in Fig. 1. All data obtained from these evaluations must be confirmed in the patient’s source documentation. All evaluations must be carried out within the time periods specified for each visit.

**Fig. 1 Fig1:**
[figure not shown]
Schedule of visits and evaluations. “^i^” indicates the following: the biochemistry of the screening visit will be valid both on the day of the screening and in the 7 days prior to the screening. “^ii^” indicates the following: the FBC of the screening visit shall be valid both on the day of the screening and in the 7 days prior to the screening visit.“^iii^” indicates the following: the coagulation of the selection visit will be valid both on the day of the selection and in the 7 days prior to it. “^iv^” indicates the following: amoxicillin/clavulanic acid 875/125 mg is to be administered according to the SmPC: 1 tablet every 8 h for 7 days. Placebo should be administered under the same conditions: 1 tablet every 8 h for 7 days

### Criteria for discontinuing or modifying allocated interventions

A patient may be removed from the study for the following reasons. However, whenever possible the patient should be followed regardless of their protocol adherence, as per the efficacy and safety evaluations:Patient withdraws consent or requests discontinuation from the study for any reasonTermination of the studyLost to follow-up

Patients who withdraw from this study or are lost to follow-up after signing the informed consent form (ICF) will not be replaced. The reason for patient discontinuation from the study will be recorded on the appropriate case report form.

### Relevant concomitant care permitted or prohibited during the trial

There is no restriction regarding the use of medications and concomitant therapies. All medications (except study medication) and nondrug therapies administered during the study should be listed in the corresponding section of the concomitant medication case report form (CRF). The use of any concomitant treatment will follow the authorized conditions of use or the standard use in clinical practice.

### Provisions for post-trial care

There is no anticipated harm and compensation for trial participation. There is no provision for post-trial care. The follow-up of patients after their participation in the trial will be conducted according to the standard clinical practice protocols at each center.

## Outcomes

### Primary outcome measure

The primary outcome measure is the percentage of patients who develop perianal fistula after surgery and during follow-up (6 months).

### Secondary outcome measures

The secondary outcome measures include the following.

#### Evaluation of the effectiveness of the intervention

Percentage of patients developing perianal fistula in the first 3 months after surgeryPercentage of patients developing perianal fistula in the first month after surgeryTime to onset of fistula (months)Complexity of the fistula according to the St James’s classificationPresence of a new episode of perianal abscess during follow-upNeed for scheduled surgery for perianal fistula treatment (number of interventions, time elapsed since initial event and technique used)Quality of life after the onset of perianal fistula

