### Sample size

To achieve 80% power to detect differences in the contrast of the null hypothesis *H*_0_:p1 = p2 using a bilateral chi-square test for two independent samples, taking into account that the significance level is 5%, and assuming that the proportion in the non-antibiotic group is 30%, the proportion in the antibiotic group is 15%, and that the proportion of experimental units in the reference group with respect to the total is 50%; it will be necessary to include 121 patients in the placebo group and 121 patients in the antibiotic group (242 patients in the study). Taking into account that the expected dropout rate is 15%, 143 patients per group would need to be enrolled, 286 patients in total.

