### Statistical methods

The statistical analysis will be carried out following the principles specified in the International Conference on Harmonization Topic E9 (CPMP/ICH/363/96). The data will be analyzed using the SPSS statistical software (version 22.0; IBM Corp).

A detailed statistical analysis plan will be available before the database is declared closed. A summary of the general approach to statistical analysis is presented. No intermediate analyses are foreseen.

A descriptive analysis will be performed for all parameters overall and by arm at every study time-point. Categorical parameters will be presented by means of frequencies and percentages. Continuous parameters will be summarized by means of the appropriate descriptive statistics (mean ± standard deviation or median and interquartile range).

The efficacy and safety endpoints will be descriptively compared between study arms. Changes from baseline, when applicable, will also be summarized by study arm.

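### Quality of life and fistula complexity exist only in patients who develop the primary outcome, so comparing them between arms is not a randomised comparison

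*Protocol article*

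**What the plan says.** In the protocol article, the subsection on evaluating the effectiveness of the intervention (under Secondary outcome measures) lists several outcomes. Two matter here: "Quality of life after the onset of perianal fistula", and the complexity of the fistula graded by St James's classification. Under Statistical methods, the article states: "The efficacy and safety endpoints will be descriptively compared between study arms". It gives no population or denominator for either outcome.

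The primary outcome is the percentage of patients who develop a perianal fistula within 6 months. The Sample size section assumes 30% with placebo ("the proportion in the non-antibiotic group is 30" per cent) and 15% with the drug ("the proportion in the antibiotic group is 15" per cent).

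The Background gives impaired quality of life as one of the burdens of fistula, and quality of life is a keyword of the article. The visit schedule is in Fig. 1, which is not shown in the text available. A detailed analysis plan is announced but is also not shown.

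**The concern.** An outcome supports a randomised comparison when it is defined for everyone randomised. These two are not. A patient without a fistula has no fistula to grade and no quality of life after its onset. The patients who enter the comparison are selected by the event the drug is supposed to prevent. If the drug works, the antibiotic arm contributes fewer patients, and they need not resemble the placebo patients with a fistula.

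Two things are at stake. First, a difference between arms in these patients may reflect which fistulas were prevented rather than what the drug did to any patient. It could flatter the drug or make it look worse. Second, the main way in which the drug could improve quality of life is by sparing patients a fistula, and a score taken only after fistula onset cannot show that. Because the outcomes stand under an effectiveness heading, readers will tend to take the by-arm figures as treatment effects.

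**Working it through.** **Inputs from the protocol article.** Sample size section: "To achieve 80% power to detect differences"; "using a bilateral chi-square test for two independent samples"; "the significance level is 5" per cent; fistula risk 30% with placebo and 15% with the drug; 121 evaluable and 143 enrolled per arm; 15% dropout. Treatment assignment method: 1:1 allocation.

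**Step 1. Reproduce the plan's own figure.** The mean risk is (0.30 + 0.15)/2 = 0.225.

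n per arm = [1.960·√(2·0.225·0.775) + 0.842·√(0.30·0.70 + 0.15·0.85)]² / (0.30 − 0.15)² = 120.5, rounded up to 121.

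For dropout, 121/0.85 = 142.4, rounded up to 143. Both figures agree with the article.

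**Step 2. Who enters the two comparisons.** Placebo: 0.30 × 121 = 36.3, about 36. Antibiotic: 0.15 × 121 = 18.2, about 18. If all 143 per arm were followed, the numbers would be about 43 and 21.

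**Step 3. Complexity.** For illustration, treat complexity as two levels, simple and complex. Let c be the share of placebo fistulas that are complex. The documents give no value for c and do not say which fistulas the drug prevents, so both are assumptions.

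*Scenario A: the drug prevents only simple fistulas.* All 15 percentage points prevented are simple, and the complex fistulas (0.30·c of randomised patients) remain in both arms. Among fistula patients the complex share is c with placebo and 0.30·c/0.15 = 2c with the drug.

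*Scenario B: prevention is unrelated to complexity.* The complex share is c in both arms. The risk per randomised patient is 0.30·c with placebo and 0.15·c with the drug.

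| c | A: complex among fistula patients, placebo vs drug | A: complex per randomised patient | B: complex among fistula patients | B: complex per randomised patient |
|---|---|---|---|---|
| 20% | 20% vs 40% | 6% vs 6% | 20% vs 20% | 6% vs 3% |
| 30% | 30% vs 60% | 9% vs 9% | 30% vs 30% | 9% vs 4.5% |
| 50% | 50% vs 100% | 15% vs 15% | 50% vs 50% | 15% vs 7.5% |

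In A the fistula-only figures suggest harm where there is none. In B they suggest no effect, although the risk of a complex fistula is halved.

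**Step 4. Quality of life.** Assume a loss of 0 points without a fistula, 10 with a simple one and 20 with a complex one, and c = 30%. These values are illustrative only.

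- Scenario A, fistula patients only. Placebo: 0.7·10 + 0.3·20 = 13.0 points lost. Drug: 0.4·10 + 0.6·20 = 16.0 points lost. The drug looks 3.0 points worse.
- Scenario A, all randomised. Placebo: 0.30·13.0 = 3.9. Drug: 0.15·16.0 = 2.4. The drug is 1.5 points better.
- Scenario A with c = 40%: 14.0 versus 18.0 among fistula patients (4.0 worse), and 4.2 versus 2.7 in all randomised (1.5 better).
- Scenario B, c = 30%. Fistula patients: 13.0 versus 13.0, no difference. All randomised: 3.9 versus 0.15·13.0 = 1.95, so the drug is 1.95 points better.

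Under these assumed losses, the fistula-only score misses the benefit of avoiding a fistula in both scenarios. Only in A does it also reverse the sign.

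**The case against.** **The comparison is only descriptive.** The article says so, and it sets out an inferential method for the primary endpoint alone. This limits the consequences, and it is why detectable differences or power for these two outcomes are not part of the argument: no test of them is planned in the article. It does not remove the problem, because the distortion comes from who is included and not from whether a p-value is printed.

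**Complexity can be graded only where there is a fistula.** Describing it in those patients is normal reporting, and a summary over all randomised patients could be set in the analysis plan from the same data. This is right, and for complexity the point comes down to denominator and labelling.

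**The quality-of-life schedule cannot be seen.** Fig. 1 may already provide for the questionnaire in everyone. A reader might infer that the trial cannot say whether antibiotics improve quality of life. The documents do not support that: they show only that the outcome, as worded, is tied to fistula onset.

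**The reversal is assumed.** A reader might also infer that the plan will make an effective drug look harmful. That requires prevention to depend on severity, on which the documents are silent. Scenario B gives no reversal.

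**Time to onset.** A reader might add this outcome to the list, on the ground that a mean or median among fistula patients would ignore those without one. The article does not restrict it to patients with a fistula. It can be analysed in all randomised patients with censoring, and that rule is commonly left to the analysis plan. It is no part of this point.

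**Conclusion.** The point holds for quality of life, by the outcome's wording, and for fistula complexity, by its nature. Their by-arm comparison is not protected by randomisation, and at the design rates it rests on about 36 versus 18 of 121 patients per arm. This much needs no assumption beyond the article's own 30% and 15%.

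The direction and size of any distortion are not known. The contrast of 30% versus 60% complex at an equal 9% per randomised patient (range 20% versus 40% to 50% versus 100%) depends on the assumed mix and on the drug preventing only simple fistulas. That the fistula-only score leaves out the gain from avoiding a fistula does not depend on this; only the size of the omission does.

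Both outcomes are secondary and compared descriptively. The primary outcome, the fistula percentages at 1 and 3 months, and the sample size are unaffected. This is a cheap improvement, not a flaw in the main result.

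**What to change.** 1. Define quality of life at a fixed follow-up time, for example 6 months, in all randomised patients, and compare the arms on that.
2. Report complexity over all randomised patients, either in ordered categories with no fistula as the best (none, simple, complex) or as the percentage of randomised patients with a complex fistula. State in advance how St James's grades map to these categories.
3. Keep summaries in fistula patients only if useful, labelled as descriptive and without a treatment-effect interpretation.

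**Cost.** The sample size does not change. Complexity needs no new data. Quality of life needs new wording and, if the schedule in Fig. 1 does not already include it, a short questionnaire for fistula-free patients at existing visits. The Trial status section describes recruitment as ongoing, with completion expected by the end of 2024. A questionnaire can be added only for patients still to enrol or in follow-up; answers not collected earlier cannot be recovered by any analysis. If that is the position, the quality-of-life result should carry the label in item 3.

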#### Safety and tolerability assessment

According to EMA recommendations (EMA/CPMP/EWP/280/96 Corr1), systemic safety shall be assessed on the basis of the adverse event record, the physical examination of patients, and the results of analytical studies.

### Sample size

To achieve 80% power to detect differences in the contrast of the null hypothesis *H*_0_:p1 = p2 using a bilateral chi-square test for two independent samples, taking into account that the significance level is 5%, and assuming that the proportion in the non-antibiotic group is 30%, the proportion in the antibiotic group is 15%, and that the proportion of experimental units in the reference group with respect to the total is 50%; it will be necessary to include 121 patients in the placebo group and 121 patients in the antibiotic group (242 patients in the study). Taking into account that the expected dropout rate is 15%, 143 patients per group would need to be enrolled, 286 patients in total.

### Data collection and management

All records will be collected in the eCRF, which will be completed by a trained and qualified investigator. Once the eCRF is completed, the original record will not be changed if any corrections are made. The completed eCRF will be reviewed by the clinical monitor.

Data entry and management will be guided by medical statistics experts. After reviewing and confirming that the established database is correct, the data will be locked by the main researchers and statistical analysts. The locked data or files will not be changed thereafter and will be submitted for statistical analysis by the research group. The Clinical Trial Unit of Instituto de Investigación Sanitaria Puerta de Hierro-Segovia de Arana, which does not have any competing interests, will be responsible for monitoring the data.

The study will be safely conducted in accordance with the protocol and applicable regulatory requirements under Good Clinical Practice, and data collection will be properly executed.

Analytical results necessary for the study will be routinely conducted in the clinical laboratories of participating centers following standard clinical practice.

